### Measures

Measurement tools and processes were identified as per the program outcomes highlighted in the Theory of Change. In discussion with the YAC, it was determined that *belonging* referred to feelings of safety and comfort associated with particular groups of people. ***Connectedness*** was similar and referred to the quality of relationships (connections) with others, especially peers. It was on this basis that the Strengths and Difficulties Questionnaire [SDQ; (36)] was used as it provides a measure of ***prosocial behaviour*** (1 subscale, 5 items) in children, adolescents and young adults. The SDQ can be administered to parents or to the young person themselves if they are aged 11 years or over. Each item is answered based on a 3-point Likert scale (not true, somewhat true, certainly true) e.g., “I am helpful if someone is hurt, upset, or feeling ill.” Scores range from 0 to 10, with higher scores indicative of greater prosocial behaviour. The SDQ prosocial subscale has fair internal consistency (*α* = 0.75) and strong test–retest reliability over 12 months (*r* = 0.64; 66). Further, the SDQ subscales have age and gender norms specific to each country (including Australia), so that scores from the sample of interest can be compared with the same population from which they were drawn. The prosocial behaviour subscale will be used to measure ***connectedness*** as it examines the young person’s ability to relate well with peers. The Longitudinal Study of Australian Children (LSAC) items that pertain to connectedness will also be used to evidence this outcome (see below discussion on deadweight for an overview of the LSAC study).

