#### Giving outcomes a value

In the final part of this process, we give the identified outcomes a monetary value using financial proxies that reflect that importance of the outcome to stakeholders (see Table 3). In consultation with the YAC, a sense of connectedness and sense of belonging was considered similar to having friends. Powedthavee (64) identified the economic value of making and having new friends, in addition to existing friends, and this value was subsequently updated and converted to Australian dollars (See Table 3). Given that the original value was calculated in 2007, we adjusted it for inflation to reflect its current purchasing power, ensuring consistency with contemporary economic conditions. Although using a currency converter may not be the ideal method, this approach, when combined with inflation adjustments, provides a reasonable approximation of the value in today’s terms.

**Table 3 tab3:** SROI stage 3 outcomes.

Stakeholder		Stage 3				
Satellite young person participants		The outcomes (what changes)				
	Outcome	How will we know if the outcome has occurred	Source	How can you value the change?	Value $AUD for six-month period	Source
		Measured how?	Where this information comes from	What proxy is used to value the change?	Value of the change	Where this information comes from
	Sense of belonging and increased connectedness	Feel more connected to other young people living in similar circumstances	SDQ: Prosocial behaviour subscale (child and parent versions) LSAC items on connectedness Interviews with children/youth	Powdthavee (64) identified the economic value of friends (in addition to existing friends): 15,500 pounds per year in 2007 is equivalent to 23,903.38 pounds in 2022, converted to 2022 AUD 42,818.76 *per annum*	$21,861.38	Powdthavee (64).
		Reduced feelings of isolation and increased feelings of belonging				
	Increased resilience	Decreased mental health crises	CYRM-R total score KCS, completed by children aged 10 years and under; CASQ, completed by older children, adolescents and young adults Interviews with children/youth	The Australian Psychological Society (APS) recommends $300 per hour per child/young person for psychological services – 14 sessions	$4,200 per child/young person	APS website: https://psychology.org.au/psychology/about-psychology/what-it-costs

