	Sense of hope, optimism and possibility	Increased hope for the future that results in planning for future activities/goals, agency	Children’s Hope Scale Interviews with children/youth	Cost of a mentor such as what might be available from the Big Brothers, Big Sisters mentoring program: $2,500 per person for 12 months	$1,250	Big Brother, Big Sisters of Australia Annual Report 2019–2020 BBBS_Annual_Report_2019-2020.pdf (bigbrothersbigsisters.org.au)

We also identified a financial proxy for resilience. For the young people involved in these programs, resilience refers to achieving positive outcomes (inclusive of wellbeing) despite coming from challenging backgrounds, and adaptively coping with current stressors (see Figure 1, Theory of Change). According to Olsson et al. (48), promoting resilience at an individual level involves developing personal coping skills and resources, both of which they suggest may be obtained from one to one therapy. Pascual-Leone et al. (49) suggested 14 individual sessions is appropriate for individuals with existing issues. It was on this basis that resilience was valued as 14 individual, psychotherapeutic sessions (see Table 3). The assumption that 14 individual psychotherapeutic sessions has a similar effect to a one-day workshop (e.g., the Create and Connect program) is admittedly contestable. However, a one-day workshop that focuses on creativity and connectedness can offer an intensive, immersive experience that might be considered similar to the impact of multiple counselling sessions (33, 50). Moreover, the unique therapeutic mechanisms of creative programs can lead to profound insights and emotional processing (51–53), potentially achieving in 1 day what might take multiple counselling sessions. The added dimension of group dynamics in these programs which emphasises peer support, can amplify the overall therapeutic impact (33, 50, 51), again potentially contributing to outcomes comparable to multiple individual counselling sessions.

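### The outcome behind about 80% of the gross unit value is priced as friendship, but the scale named to measure it scores prosocial behaviour, and no source is named as deciding

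*Protocol article*

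**What the plan says.** **Definition.** The Measures section of the Protocol article takes belonging to be feeling safe and at ease with a group, and connectedness to be how good one's relationships are, chiefly with peers. Table 3 gives the signs of success as feeling more connected to young people in like circumstances and "Reduced feelings of isolation and increased feelings of belonging".

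**Price.** Under Giving outcomes a value, the youth council's view is reported: "a sense of connectedness and sense of belonging was considered similar to having friends". The proxy is a published value of additional friends: 15,500 pounds a year in 2007 "is equivalent to 23,903.38 pounds in 2022, converted to 2022 AUD 42,818.76" per year. It is entered as $21,861.38 for six months.

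**Measure.** "The prosocial behaviour subscale will be used to measure" connectedness, on the ground that it looks at how well the young person can get on with peers. The score runs from 0 to 10, and higher means more prosocial behaviour. The one item shown is "I am helpful if someone is hurt, upset, or feeling ill". Parents can complete it, and young people can do so themselves from age 11. LSAC "items that pertain to connectedness will also be used to evidence this outcome", and Table 3 also lists interviews.

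**Deadweight.** Under Deadweight and displacement, LSAC items on connectedness and belonging serve as a benchmark, with comparison data only from age 14. Interview answers qualify that comparison and supply deadweight for other ages and outcomes.

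**The concern.** What is valued is a state of the participant's relationships: having friends, feeling less alone, belonging. What the named scale scores is conduct towards others. The two can move apart. A participant can make lasting friends without becoming more helpful, or become more helpful without gaining a friend. The Introduction says that many of these young people are carers and that many name compassion as a positive outcome. Helpfulness may therefore already be high at entry, leaving little room on a 0 to 10 scale for a real gain to show. That is an inference; the article gives no baseline scores.

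Three sources are listed without an order of precedence, so the largest amount in the calculation could be credited or withheld depending on which source the analyst relies on. If the prosocial score were that source, its change would be reduced by a deadweight fraction obtained in another way.

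**Working it through.** **1. Inputs, all from Table 3.** Friendship: $21,861.38 for six months as printed, from $42,818.76 a year. Resilience: 14 sessions at $300, printed as $"4,200 per child/young person". Hope: $"2,500 per person for 12 months", entered as $1,250.

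**2. Reproducing the six-month values.**
- Friendship: 42,818.76 / 2 = 21,409.38. The printed figure is 21,861.38, which is 452.00 higher (452.00 / 21,409.38 = 2.1%), so it does not reproduce.
- Resilience: 14 × 300 = 4,200, which reproduces.
- Hope: 2,500 / 2 = 1,250, which reproduces.

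**3. Share of the gross unit value.** Share = friendship / (friendship + resilience + hope), per participant, before deadweight, attribution, displacement and drop-off, with each outcome credited equally often.
- Printed value: 21,861.38 / (21,861.38 + 4,200 + 1,250) = 21,861.38 / 27,311.38 = 80.0%. Resilience is 15.4% and hope 4.6%.
- Halved annual value: 21,409.38 / 26,859.38 = 79.7%.

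The $452 discrepancy does not change the conclusion.

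**4. What rests on the crediting decision (illustration).** Assume the other two outcomes are credited in full.
- Half of the friendship value credited: 10,930.69 + 5,450 = 16,380.69, or 60.0% of 27,311.38.
- A quarter credited: 5,465.35 + 5,450 = 10,915.35, or 40.0%.

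For comparison, the planned ±10% change applied to the friendship value moves the total by 2,186.14 / 27,311.38 = 8.0%.

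**5. Evidence and deadweight side by side.**

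| Age | Evidence of change | Deadweight source |
|---|---|---|
| 14 and above | SDQ prosocial, LSAC items, interviews | LSAC items, qualified by interviews |
| Below 14 | SDQ prosocial (parent report below 11), interviews; LSAC items if asked | Interviews |

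From 14, outcome and deadweight can be put on the same LSAC items, but the article does not say that they will be. Below 14 the only benchmark is the interview estimate. In neither row is deadweight measured on the prosocial scale.

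**The case against.** The prosocial subscale is not the sole evidence. LSAC connectedness items and interviews are named for the same outcome, Table 3 ranks none of them, and the design integrates quantitative and qualitative results. A reader might infer that the friendship credit is granted or refused on the SDQ score alone. The article does not say so, because it gives no rule for turning any score into credited participants.

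A reader might also infer that a deadweight percentage from LSAC items must be deducted from change on the SDQ. That does not follow either. LSAC is described as one of several routes, interviews cover the other ages, and a like-for-like LSAC comparison is open from age 14.

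On validity, only one of the five items is shown, the article gives a reason for its choice, and the youth council advised on instruments. To say that the subscale measures nothing of connectedness would go beyond what the document can settle.

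These points stand and limit the finding. They do not answer it. The subscale is still the scale named for connectedness, and the article's own reading of its score differs from its own definition of the outcome. The order of precedence is unstated. The Limitations section does not raise the mismatch. The sensitivity analysis varies the values of assumptions and is not described as comparing indicators.

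**Conclusion.** The point holds as one of fit and precedence. The outcome with about 80% of the gross unit value (80.0% as printed, 79.7% with the annual figure halved) is defined and priced as relationships and friends. The scale named for it indicates helping behaviour, and the plan does not say which of its three sources decides.

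The 80% is a share of unadjusted unit values with equal crediting. It is not a share of the final ratio, which depends on how many participants are credited and on the discounts. The direction and size of any resulting error cannot be derived from the document, since it reports no relation between the prosocial score and connectedness. This is a change that should be made, at low cost, and not a flaw that invalidates the evaluation.

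**What to change.** - State that the LSAC connectedness items decide the friendship credit for every participant able to self-report them.
- From age 14, use those same items for both the outcome and the deadweight.
- Keep the SDQ prosocial subscale as supportive evidence.
- Report participants below 14 separately. Where they can answer the LSAC items, those decide the credit and deadweight stays with the interview estimate. For children too young for the items, base both credit and deadweight on interviews, and label parent-reported SDQ as indirect evidence.
- Reconcile the $21,861.38 with half of $42,818.76.

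**Cost.** This changes the roles of measures already planned and needs no new instrument. The team should check which ages are being asked the LSAC items, as the article does not say. The main downside is below 14, where no LSAC benchmark exists. Interviews are also few: seven to nine per program gives 14 to 18 for the two programs that admit children, and not all of those will be young. Nine longitudinal participants are spread over all three programs. The credit for younger children will therefore be less certain, and the report should say so.

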### Conversations with young people

Individual ***conversations*** with young people/children will also be conducted as another way of evidencing all three outcomes. The YAC recommended calling the interviews “conversations” to be less formal and intimating and that is the language we use here also. Seven to nine young people from each of the identified programs will be invited to a conversation about their experiences of the programs, and self-perceived outcomes, both positive and negative. We anticipate up to one hour for these conversations and with parental and child consent they will be audio-recorded. Transcripts will be analysed within an inductive qualitative paradigm, using the six-step reflexive thematic process recommended by Braun and Clarke (44, 45) which involves becoming familiar with the data, generating initial codes, searching for and reviewing the themes, and then defining and naming the themes.

In addition, we will conduct ***longitudinal conversations***, at three time points with the same nine participants, over the duration of the project. Participants will be drawn from across the three identified programs. Given that many young people attend more than one program, these conversations will allow us to explore the cumulative impact of Satellite’s offerings, looking for instances of continuity, change and growth over time (46). Those who discontinue their relationship with Satellite will also be invited to be interviewed, to ascertain the reasons why they have disengaged, and what impacts may have occurred and remain (if any) from program participation. A within-case analysis will be conducted within each conversation data set, followed by a cross-case analysis of patterns that may occur over time and across conversations (46). All conversation schedules were developed with the YAC to ensure that the language was strength-based and age-appropriate and that content aligned with preferred program outcomes.

### Data analysis

The findings from both quantitative and qualitative components of the project will be integrated following separate analysis using a mixed methods approach adapted from Lieber’s (47) conceptual model. Qualitative interview data from the various stakeholder populations will initially be analysed thematically (44) while quantitative data will be analysed via traditional methods including repeated-measures MANCOVA. Following these two separate processes, the categorical dimensions of the qualitative themes will be developed, which are ‘grounded’ in the raw data (47) through a process of constant comparative analysis and robust discussion amongst the research team. These grounded dimensions will then be integrated with the results from the quantitative data, with the analysis process facilitating meaning making of the quantitative data that describes the factors and/or circumstances (e.g., age, program type and ‘dosage’, cultural background, gender) that may be associated with various outcomes, incorporating also stakeholders’ perspectives (the YAC and Satellite management) on why and how these outcomes were delivered.

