Parents or guardians of participants are informants on children’s progress and outcomes but not involved as targets of change in the programs. Another stakeholder is governments which provide services that may experience reduced demand as a result of benefits experienced by the children and young people. Guided by the social value principles, all stakeholders who experience change—positive or negative, intended or unintended—should be considered in the analysis. Nonetheless, to keep the SROI feasible and replicable, it was decided by the research team and Satellite management that the SROI focus on children and young people only. By focusing exclusively on children and young people, the SROI analysis can accurately capture the specific benefits and outcomes relevant to this demographic (23). This focus also allows for direct engagement with the primary end users, (namely young people) whose perspectives and experiences can be systematically and exclusively included in the analysis. It is acknowledged that the omission of other stakeholders who may be experiencing outcomes from the SROI may result in a devaluing of the programs. The SROI focus on three representative, capstone programs including:

Satellite Camp for 8-12-year olds.Create and Connect for 8-17-year olds.Satellite Connect for 18-25-year olds (see Table 1 for more detail).

**Table 1 tab1:** Satellite programs.

Programs	Participants’ ages (approx.)	Brief description
Satellite Camps	8–15	Satellite Camp is a three-day overnight program for young people with family members who experience mental health challenges, giving them the opportunity for respite from their caring role. It aims to improve young people’s confidence, develop new skills and establish meaningful connections with other young participants who come from similar families. There is a mix of engaging outdoor and indoor creative activities that create a fun and safe environment for building skills and confidence, while making peer connections with other young people living with similar families. Camp facilitators provide role modelling for adaptive coping and normalising conversations about mental illness.

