Create and Connect	8–17	These workshops are one-day programs that offer opportunities for participants to connect with peers in a safe, creative space. Various workshops are offered including music and song writing, photography and visual art such as graffiti and meme-making, plus other art and craft-based activities. Participants learn how to use music, photography, and art to express themselves, in an environment where they have the opportunity to connect with other young people who have a family member living with mental health challenges. The workshop allows participants to explore their personal and shared experiences through open dialogue and develop inclusive communication skills, including both visual and spoken language.
Satellite Connect in person or online	18–25	A structured peer support and peer development program that gives young people the space to be heard, learn new skills, and share their stories. Also covered is how their lived experience might be used to positively shape and influence the lives of younger children. Online versions of Satellite Connect run for 6 weeks, while in-person editions of Satellite Connect takes place across 3 weeks. During the program, participants meet other young people who have a family member living with mental health challenges, and interact, collaborate, and form connections with others living with similar families. Various themes are discussed including self-care and self-compassion, communicating creatively, talking about mental health, mental illness, language and stigma, and considering next steps for participants to practice newly acquired skills.

These programs were selected because they provide a good overview of participants’ ages and represent the capstone programs offered to young carers. Given they attract the most participants, this focus also provides rich data for analysis. The SROI covers the period of January 2023 through to June/July, 2024 with the final evaluation report to be delivered in August 2024.

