## Evidencing outcomes and giving them a value

### Evidencing outcomes

This stage involves finding data that demonstrates whether preferred outcomes have occurred and then valuing those outcomes. A convergent parallel mixed method approach will be employed, consisting of qualitative and quantitative data collection and analysis and then comparing and relating the two before interpreting them (34).

All participants will be asked demographic questions about their age, gender identity, cultural background, language spoken at home and the nature of their family member’s illness. They will also be asked which Satellite program/s they have been involved in.

For the quantitative component of the evaluation, a within-subject pre-post study design will be used to identify potential changes over time (35). Accordingly, participants (and their parents, for children aged 18 years and under) in targeted programs will be invited to participate in questionnaires on program entry, and then 6 months later, using the number of programs as a covariate (as some will attend multiple programs). Participants are asked to record a nickname when completing questionnaires, to ensure traceability across time one and two (pre and post). Individual and longitudinal conversations will also be employed. Further detail for these steps is presented below.

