An *a priori* power analysis was conducted using G*Power version 3.1.9.7 software (65) to determine the minimum sample size required for the study. The required sample size to achieve 80% power for detecting a medium effect at a significance criterion of *α* = 0.05 will be 29 per group {intervention [Satellite participants] and usual care [LSAC]; as per (30)}. Other deadweight measures will be ascertained by asking young people what they perceive would have happened if they had not attended Satellite and their estimation of the impact of that occurrence (in the interviews). This is necessary as there is a risk that LSAC participants may be engaged in programs similar to Satellite. Their responses will be used to inform and qualify any differences between the LSAC calculations and the Satellite participant sample as well as deadweight across other age groups and for other outcome measures not included in the LSAC data set.

Displacement is an assessment of how much the outcome might have displaced other outcomes, including the occurrence of negative outcomes for the children and young people and others. An evaluation of a similar program {Paying Attention to Self [PATS]; (57)} found that building new connections with participants during the program came at the cost of building peer relationships in other sites outside the program such as school and this is a concern that could apply here. Alternatively, participants could be gaining transferrable social skills at Satellite that then lead to better connections at school and other settings. We will be investigating this and other potential outcomes in the conversations with young people and who they are turning to.

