## Limitations

A potential limitation inherent in any SROI study is the monetisation of outcomes (28) and a lack of a universal bank of indicators (59). However, even those things with a market value are valued subjectively based on market conditions and consumer preferences. It was challenging to identify financial proxies for the various outcomes in this study, especially in relation to resilience as it comprised of multiple factors. As pointed out by Mook et al. (60), the choice of financial proxies can become subjective, which can compromise the reliability of the SROI. Given these challenges, Nicholls et al. (26) highlighted the importance of being transparent about the development and identification of these proxies which this protocol aims to do. Nonetheless, we agree with the notion purported by Arvidson et al. [(23), p. 233] when they argued that excluding significant outcomes which may be challenging to place a monetary value on, would “render the analysis precisely wrong, rather than the desirable “roughly right” and would greatly diminish the perceived social value of a given program.

We acknowledge the relatively short-term nature of the study and our subsequent inability to track long term change (or lack thereof). The study would have been strengthened had we been able to locate a comparison group for children under 14 years of age and for other outcomes besides connectedness. Using a currency converter to update the 2007 value of friendships presents a limitation in our analysis and may not fully capture more nuanced economic changes over time. We also acknowledge that the decision to aggregate the number of programs without employing a weighting system may limit the analysis. Similarly, the various programs offered by Satellite are delivered by different facilitators. As the knowledge, experience, skill and interpersonal style of group facilitators can have a significant impact on program outcomes (61), it will be difficult to determine which specific program/s are responsible for participant outcomes. Nonetheless, we are collecting fidelity logbooks to document the consistency of program delivery (30).

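### The named repeated-measures MANCOVA has no term for shared program session or facilitator, so standard errors for pre-post change may be too small

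*Protocol article*

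**What the plan says.** The Data analysis section of the protocol article states that "quantitative data will be analysed via traditional methods including repeated-measures MANCOVA". The Evidencing outcomes section sets the design: "a within-subject pre-post study design will be used to identify potential changes over time", with questionnaires at program entry and six months later, "using the number of programs as a covariate (as some will attend multiple programs". The Attribution section adds control for earlier Satellite participation and for use of carer services or health professionals. All of these adjustments are at the level of the individual.

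Delivery is to groups. In Table 1 (Establishing scope and identifying stakeholders), "Satellite Camp is a three-day overnight program for young people with family members who experience mental health challenges", and of Create and Connect it says "These workshops are one-day programs that offer opportunities for participants to connect with peers in a safe, creative space". Satellite Connect is described there as a peer support program. Giving outcomes a value credits group dynamics with adding to the therapeutic effect. The Limitations section says that "the various programs offered by Satellite are delivered by different facilitators" and that the "interpersonal style of group facilitators can have a significant impact on program outcomes".

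Under Deadweight and displacement, the sample size for comparing Satellite participants with LSAC participants "will be 29 per group", for 80% power, a medium effect and alpha 0.05. The article does not mention clustering, an intra-group correlation, a random effect or robust standard errors.

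**The concern.** The repeated-measures part of a MANCOVA deals with two measurements on the same person. It does nothing for two people who attended the same camp, workshop or peer group under the same facilitators. The baseline is taken at program entry, so whatever a session contributes appears after baseline, in the change score. If good sessions lift all their members and weak ones lift none, change scores within a session are positively correlated, and an analysis that ignores this overstates its precision.

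Connectedness is the outcome most exposed. It concerns relationships with peers, carries the largest monetary proxy in Table 3, and is the only outcome compared with LSAC. At stake is the inference that change occurred, and that it exceeded change in the comparison group. A false-positive change becomes more likely than the nominal 5%.

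**Working it through.** **The plan's own figure.** The 29 per group cannot be reproduced uniquely, because the article does not give the test, the effect-size metric, sidedness or the pre-post correlation. Some candidates for 80% power at alpha 0.05:

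- Two-sample t test, d = 0.5: 64 per group two-sided, 51 one-sided. Power at 29 per group is 46% and 59%.
- Within-between repeated measures, two groups by two times, f = 0.25: 34 in total at correlation 0.5, 59 in total at correlation 0.1.
- Single-predictor regression, f² = 0.15: 55 in total, about 28 per group.
- ANCOVA, d = 0.5, pre-post correlation 0.75: 28 per group.

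A few come close to 29, but only with inputs the article does not state. All treat participants as independent, and none contains a design effect.

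**Inputs for clustering.** The article gives neither group size (m) nor intra-group correlation of change (ICC). Assumed ranges: m = 8 to 15, ICC = 0.02 to 0.10.

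**Formulas.**

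- Design effect when all participants are clustered (pre-post change): DE = 1 + (m − 1) × ICC.
- True standard error relative to the naive one: √DE.
- Actual two-sided error of a nominal 5% test: 2 × [1 − Φ(1.96/√DE)].
- Information in 29 participants: 29/DE.
- LSAC comparison, Satellite arm clustered only, equal arms and variances: variance inflation (1 + DE)/2, used in place of DE in the error formula.

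| m | ICC | DE | √DE | Error, pre-post | 29/DE | (1+DE)/2 | Error, LSAC |
|---|---|---|---|---|---|---|---|
| 8 | 0.02 | 1.14 | 1.07 | 6.6% | 25.4 | 1.07 | 5.8% |
| 15 | 0.02 | 1.28 | 1.13 | 8.3% | 22.7 | 1.14 | 6.6% |
| 8 | 0.10 | 1.70 | 1.30 | 13.3% | 17.1 | 1.35 | 9.2% |
| 15 | 0.10 | 2.40 | 1.55 | 20.6% | 12.1 | 1.70 | 13.3% |

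Example: m = 15, ICC = 0.10 gives DE = 1 + 14 × 0.10 = 2.40, √2.40 = 1.55, 1.96/1.55 = 1.265, and 2 × [1 − Φ(1.265)] = 0.206. At m = 8 and ICC = 0.01, DE is only 1.07 and the pre-post error 5.8%, so a negligible effect is also possible.

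**Which cluster term is needed.** Write the score of person i in session g at time t as μ_t + s_g + p_i + e_igt. The change is (μ_2 − μ_1) + (e_ig2 − e_ig1): the session intercept s_g and the person intercept p_i both cancel. A model with only those intercepts therefore gives the same precision for change as the naive analysis. The session must act on change: μ_2 − μ_1 + c_g + error, with c_g the session-by-time effect. A small simulation agrees (12 sessions of 10, change ICC 0.10, no true change, 150 runs): the paired test and the random-intercept model both rejected in 18%. The formula gives 15.5% there (DE = 1.90), with a simulation standard error of √(0.155 × 0.845/150) = 3.0 percentage points.

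**The case against.** The strongest reply is that this is an article, not the full plan. Its list of methods is open-ended, fuller evaluation detail is referred to a companion publication that is not shown, and random effects or robust errors are ordinary analysis-plan content. That stands in part: clustering may be handled elsewhere. But the article does name a test and several adjustments, and what it names does not fit the delivery it describes.

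It can also be said that shared delivery is disclosed. Limitations mentions differing facilitators and fidelity logbooks, and Data analysis mentions program type and dosage. These bear on which program produced an outcome. They do not correct a standard error.

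Three points on size stand. The relevant correlation is that of six-month change, which may be small. Young people may attend several programs, so group membership overlaps and the design effect is approximate. LSAC data cover only ages 14 and above and only some Satellite participants are matched, so the number of matched participants per session may be below attendance.

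A reader might also infer more than the article supports:

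- *Siblings attend together.* Siblings appear only as the family member with mental health challenges. Nothing says that they enrol jointly.
- *Standard errors will certainly be too small.* That needs a positive within-session correlation of change, for which no figure is given.
- *The SROI ratio is inflated.* Clustering mainly affects standard errors, not point estimates. Calculating the SROI makes no p-value a condition for entering the ratio. Interviews also evidence all three outcomes, and they inform deadweight where LSAC has no data.

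**Conclusion.** The point holds as a mismatch between the one named method and group delivery. The article's own statements on group dynamics and facilitators make independence between participants doubtful, and none of the stated covariates represents session or facilitator. Under the assumed ranges, true standard errors for pre-post change are 7% to 55% larger than the naive ones and the actual error rate is about 7% to 21%. For the LSAC comparison the rate is about 6% to 13%. A fully clustered Satellite arm of 29 would carry the information of about 12 to 25 independent participants. These figures rest on assumed group sizes and correlations, equal arms and variances, a normal approximation and one session per person. The harm falls on the pre-post and LSAC inferences; no direct effect on the ratio is shown.

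**What to change.** Have participants record their entry session on the questionnaire themselves. Questionnaires are linked by nickname and Satellite staff are not told who takes part (Ethics statement), so the item should not depend on matching to Satellite's records.

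Analyse each outcome with one of the following:

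- cluster-robust standard errors by entry session, with a small-sample correction; or
- a mixed model with a session-by-time random effect, not session intercepts alone.

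Treat multiple attendance by stating that clustering on entry session is an approximation, or by a sensitivity analysis. In the LSAC comparison, model clustering in the Satellite arm only. If 29 matched participants came from full groups of 8 to 15, that would be only about two to four sessions (29/15 = 1.9, 29/8 = 3.6). With so few sessions, report the limit on precision. Add a family term only if siblings are found to take part together.

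Cost: one extra questionnaire item, a modest change to the analysis, and somewhat wider intervals. Label: Cheap improvement.
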